All statistical tests for the before intervention period will be two-sided but all tests of whether the intervention made a difference will involve a one-tailed matched pair t-test, and either a p value of 0.05 or less will be used to indicate statistical significance or a confidence interval will be provided to judge the impact of the intervention. Statistical analysis will be performed using Stata Release V.12 (TX: StataCorp LP), SPSS 17, R package [38] and Microsoft Excel.

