### Classical BACI designs and extensions

Because of the temporal nature of health data and the underlying trends caused by the increasing burden of chronic disease with increasing age, before and after comparisons can be difficult or inconclusive. In this study we will have available patient data for a period of 4.5 years including the period of the intervention which may vary from 6–18 months.

Since standard BACI design cannot be used when study variables trend over time, we adopt a mathematical approach using a mixed linear effects model (*lme*) to assess the intervention while trying to adjust for the time varying mean in simple ways. The *nlme* library in the statistical package R is used to perform the analysis according to the methods of Pinheiro et al. [39].

The Test patients will be matched with one or two controls and the relative movement of Test patients’ outcomes before and after the start of the intervention will be compared to that of their Control patients. The before-and-after comparisons use control patients to adjust for background variations in such variables as public health policy impacting on costs and even for example, climatic conditions during the before and after intervention period.

Let *y*_*ijk*_ be any of the variables to be analysed, such as for example, the PBS/MBS/Hospital costs value per unit time period (month) at time k during period *i* (before or after the intervention), for patient *j* (control or intervention patient). The model for the response value is given by

where:

 *μ* is the overall mean *α*_*i*_ is the effect of period (before and after) τ_k(i)_ is the repeated measures within periods (assumed to be a random effect) β_j_ is the effect on jth matched patients (intervention or control) (αβ)_ij_ is the interaction between period and matched patient groups θ is the overall slope relating to time in months if no differentiation is made between the groups (B-A, C-I) θ_ij_ is the slope relating to time (k) in months for the various combinations of the groups (B-A, C-I). e_ijk_ is the random error term of the model that is assumed to be normally distributed with homogeneous variance.

Assumptions made:

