 Log of cost plus one will be treated as normally distributed with log of the number of days in the month as the offset. Sometimes the square root transformation may be used to stabilise the variance. We are hoping there are not too many zero cost periods or zero counts. If this fails we will use the zero adjusted inverse Gaussian distribution for the model – fitting them using the **gamlss** (package in R) using random() for including random effects [40]. τ_k(i)_ is a random effect in the above model that is assumed to be normally distributed with mean zero and constant variance. The assumption in the previous dot point and the assumption for e_ijk_ in the model thus assumes that measurements made at the same time segments (e.g., on the same quarter) have the same correlation and homogeneous variances for all repeated measures. The above model treats the study as a fully-designed experiment with the appropriate randomisation. However, this is seldom the case because most impact studies are observational in nature. The assumption is that each measurement for the intervention patients is matched with a measurement for one or more control patients. This blocking is expected to control for the non-randomisation in the design. The complexity of this analysis can be greatly reduced by taking the differences between the Test and Control measurements The model above tests whether a significant change has occurred by testing the significance of the interaction term of the model for the before after indicator variables and the control-intervention indictor variable. For example if the coefficient for intervention patients and after intervention duration has lower insured costs that before the intervention after adjusting for controls, then the intervention has had a significant impact on costs. The random effects terms and random error term are assumed to be uncorrelated in time. The control patient is generally selected to control for all covariates. In this study this means that control patients should be identical to the intervention patient in terms of age, gender, SEIFA index and major comorbidities. The samples are selected over time (therefore they are time series rather than repeated measures made at the same time). So it may seem unlikely that the model errors will be independently distributed but hospital costs are measured a month apart and this should be enough to for the assumption of independence to be valid. The assumption that all repeated measures have the same variance is unlikely to be true. If the gamlss package is used then this change in variance can be accounted for. Although theoretically longitudinal data structures can be modelled by random effects in gamlss [40] but at present no computationally feasible implementation for large sample sizes and complex models exists. Assume that the trend in the response variable over time is approximately linear. This assumption is likely to be reasonable over the 5 year study period, but is unlikely to be true for longer time periods.

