**Figure 5 Fig5:**
[figure not shown]
**Output of lme modelling of mean monthly MBS cost per patient for test and control.** Patients based on hypothetical data. Each monthly data point is plotted as a box and whiskers plot representing data for the 125 Test patients and 250 Control patients.

The BACI analysis will be carried out using the statistical modelling package R [38]. The output will provide an estimate of the correlation between Test and Control data and will provide best fits, standard errors, t-values and p-values for all model parameters before and after the intervention.

In the schematic diagram above we would expect very little difference between Test and Control patients in either the slope or the intercept of the model prior to the start of the intervention. The hypothetical model in Figure 5 shows that the impact will result in a change of the historical slope of the model before the intervention for Test patients, representing a time dependent fall in Mean Monthly MBS Costs, whilst there is no corresponding change in the slope for Control patients after the intervention.

Modelling of the available data will reveal underlying time dependent trends associated with the ageing process as well as the impact of the intervention and will allow an estimate to be made of savings associated with the impact of the intervention.

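### The declared model test is a level interaction at time zero, but the expected effect is a change of slope, so the test can miss it or, under one time coding, reverse its sign

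*Protocol article*

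**What the plan says.** Four statements in the protocol article bear on this point.

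- **The model** (Classical BACI designs and extensions). The listed terms include (αβ)_ij, which "is the interaction between period and matched patient groups", and θ_ij, which "is the slope relating to time (k) in months for the various combinations of the groups (B-A, C-I". So the model has both a level interaction and a slope for each of the four period-by-group cells.
- **The decision rule** (same section, list of assumptions). A significant change is judged by "testing the significance of the interaction term of the model for the before after indicator variables and the control-intervention indictor variable". The worked reading is that "if the coefficient for intervention patients and after intervention duration has lower insured costs that before the intervention after adjusting for controls", then there has been a significant impact on costs.
- **The expected effect** (text after Figure 5). Before the start, "we would expect very little difference between Test and Control patients in either the slope or the intercept". Afterwards, "the impact will result in a change of the historical slope of the model before the intervention for Test patients", "whilst there is no corresponding change in the slope for Control patients after the intervention".
- **A second test** (Data analysis). Here "all tests of whether the intervention made a difference will involve a one-tailed matched pair t-test", at a p value of 0.05 or less or with a confidence interval.

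The article does not say from which month k is counted. The model equation itself did not survive in the text available for this review, so the term list is the evidence for its structure.

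**The concern.** The article leaves the standard BACI comparison because outcomes trend over time, and it adds slopes to deal with that. It then attaches the decision to the term for two indicator variables, which is the level term. Once every period-by-group cell has its own slope, that term no longer measures the effect over the after period. It measures the gap between the fitted lines at one point in time, month zero. The effect drawn in Figure 5 sits in the slopes.

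At stake is the main conclusion on costs and service use. A real fall that builds up gradually could be reported as no impact. Under one coding of time it could give a coefficient pointing to a rise. The result of the declared test would depend on how months are numbered, which should not matter.

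**Working it through.** The plan gives no figure for the power of the interaction test, so there is none to reproduce. Table 6 concerns a paired t-test with an effective sample size of 30, and no numerical σ or ρ is available in the text.

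**Step 1: the coefficient, without noise.** Let D_k be the Test-minus-Control difference in month k of the record. Following Figure 5, set D_k = 0 before the start T0 and D_k = d·(k − T0) after it, with d < 0 for a fall. If the model's time variable is t = k − c (origin at month c), the after-period line is d·t − d·(T0 − c). Hence:

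- slope interaction = d, whatever the origin;
- level interaction = −d·(T0 − c), which depends on the origin.

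The article gives 4.5 years (54 months) of data, of which 6 to 18 months follow the start. So T0 = 48, 42 or 36. With d = −1 per month:

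| Origin of k | 6 months after | 12 after | 18 after |
|---|---|---|---|
| Start of record (c = 0) | +48 | +42 | +36 |
| Mean of record (c = 27.5) | +20.5 | +14.5 | +8.5 |
| Start of intervention (c = T0), or restart in each period | 0 | 0 | 0 |
| End of record (c = 54) | −6 | −12 | −18 |
| Slope interaction, any origin | −1 | −1 | −1 |

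A least-squares fit to these series returned the same values. The restart row relies on the expected absence of a difference before the start. If the θ_ij were left out, the level term would have the right sign (−3.5, −6.5, −9.5), but that is not the model listed.

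**Step 2: power, for illustration.** The sample sizes, 125 and 250, are the article's. The rest is assumed: 42 months before and 12 after (k = 0 to 53), residual SD 1, independent errors as the article assumes, and a pure slope change with a mean after-period fall of 0.15. A patient's own constant level cancels in before-after contrasts.

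- Variance of a monthly group difference: 1/125 + 1/250 = 0.012.
- Before: mean k = 20.5, Sxx = 6170.5. After: mean k = 47.5, Sxx = 143.
- Slope change: the mean distance from the start is 5.5 months, so d = −0.15/5.5 = −0.0273.

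*Level test, origin at the start of the record.* Coefficient = 42 × 0.0273 = +1.15. SE = √[0.012 × (1/42 + 20.5²/6170.5 + 1/12 + 47.5²/143)] = 0.4375. z = +2.62. The chance of a one-sided significant fall is Φ(−2.62 − 1.645), about 0%. The chance of a nominally significant rise is Φ(2.62 − 1.645) = 83% one-sided, or Φ(2.62 − 1.96), about 75%, at the two-sided 5% level.

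*Level test, origin at the start of the intervention.* Coefficient = 0, so power equals the 5% test size.

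*Change averaged over the after period.* SE = √[0.012 × (1/12 + 1/42 + (47.5 − 20.5)²/6170.5)] = 0.0520. z = 0.15/0.0520 = 2.885. Power = Φ(2.885 − 1.645) = 89%. A mean fall of 0.10 gives 61%, and 0.20 gives 99%. None of these depends on the origin.

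**Step 3: sensitivity to the SD.** With residual SD 2, the averaged contrast has 42% power and the one-sided wrong-direction rate is 37%. The coefficients in Step 1 do not change.

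**The case against.** **The wrong sign is not established.** It needs k to run from the start of the record. The article speaks of time k during period i and nests the repeated-measures term within period, which leans towards a restart in each period. The coefficient is then zero, not reversed. An origin at the end of follow-up would even give the right sign. This stands: a reader might infer that the analysis will report a rise, but the document supports only that it can. The restart reading does not rescue the test, because a zero coefficient leaves it with power equal to its size.

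**The slopes will be reported.** The text after Figure 5 promises p-values for all model parameters, so a slope change would be visible. This also stands, and it rules out the reading that the whole analysis is blind to the effect. But a printed parameter is not the declared test, and choosing between level and slope after seeing both would be post hoc.

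**A declared t-test can detect the effect.** In the scenario above, a comparison of after-minus-before means has SE √[0.012 × (1/12 + 1/42)] = 0.0359 and power of about 99%. After-period means alone, with an assumed between-patient SD of 0.65, have SE √[0.012 × (0.65² + 1/12)] = 0.0779 and about 61%. Both ignore any gain from matching, and the article does not say which is meant. So it is fair to say that another declared test could find the effect. That leaves two declared tests that can disagree. It is tempting to count three, but the slope change in Figure 5 is an expectation, not a decision rule.

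**Figure 5 is hypothetical and covers MBS costs only.** True, and an immediate level shift would be picked up by the level term with the origin at the intervention. Still, a slope change is the form of effect that the article itself describes.

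**The full protocol or analysis plan may settle the origin.** It may. The point does not rest on that omission: the stated rule does not match the stated model and expected effect.

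**Conclusion.** The concern holds in a limited form. The decision rule names the level interaction, while the listed model and the expected effect place the impact in the slopes. For a pure slope change the level coefficient is zero with time counted from the intervention or restarted in each period, and has the wrong sign with time counted from the start of the record. This is algebra and needs no assumed SD. It does rest on the term list, on a pure slope change and on no difference before the start.

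The power figures (5% or 0%, against about 89%) are illustrative and fall or rise with the assumed SD and effect size. The 83% should not be read as a likely false claim of harm: with tests that are one-tailed for benefit, that result would be read as no benefit. The accurate statement is that the declared model test can miss the expected effect, and that the article does not say whether this test or the matched-pair t-test decides.

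**What to change.** In Classical BACI designs and extensions, count time as months from the start of the intervention. Replace the indicator-interaction test with one pre-named contrast that includes the slope change: the Test-minus-Control change averaged over the after period, with its confidence interval. With time so coded, this is the level interaction plus the slope interaction multiplied by the mean after-period month.

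In Data analysis, reconcile the blanket matched-pair t-test statement with the model section by saying which test decides. The choice needs care, because the article rests the validity of its comparisons and Table 6 on the paired test. Making that test merely supportive, or adding a joint two-degree-of-freedom test (which has no one-sided form), is a separate and debatable step that this fix does not need.

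The cost is wording and a contrast statement in the same model, with no new data. The Table 6 power must then be described as applying to the paired t-test only.

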**Methods/Design:**

A clinical trial is proposed at five locations in five states and territories along the Eastern Seaboard of Australia. Each site will have 25 Test patients and 50 case matched control patients. All participants will be selected based on clinical criteria of at least two hospitalisations in the previous year or four or more admissions over the last five years for a range of one or more chronic conditions. Control patients are matched according to age, sex, major diagnosis and their Socio-Economic Indexes for Areas (SEIFA). The Trial Design is an Intervention control study based on the Before-After-Control-Impact (BACI) design.

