**Table 1 Tab1:** **Clinical criteria for eligibility**

Criteria	Type	Description
Age	Inclusion	50 years old and over at consent.
Cognitive capacity	Inclusion	Abbreviated Mental Test (AMT) [23] score >7.
Unplanned acute admissions	Inclusion	A rate of unplanned acute admission with the required principal diagnosis code(s) indicated below:
		a) ≥2 in the last 12 months, or
		b) ≥4 in the previous 5 years.
ICD-10-AM principal diagnosis code(s) for each unplanned acute admission	Inclusion	Code(s) for each unplanned acute admission indicate a diagnosis for one or more of the following chronic conditions:
		a) Chronic Obstructive Pulmonary Disease (J41 – J44, J47 and J20, with secondary diagnosis of J41-J44, J47),
		b) Coronary Artery Disease (I20 – I25),
		c) Hypertensive Diseases (I10 – I15, I11.9. Note: Hypertensive Heart Failure (I11.0) is included in Congestive Heart Failure),
		d) Congestive Heart Failure (I11.0, I50, J81),
		e) Diabetes (E10 - E14),
		f) Asthma (J45).
Unsuitable conditions	Exclusion	The study team considers the presence of the following conditions to be unsuitable for participation in the study:
		a) Any form of cancer,
		b) Any neuromuscular disease
		c) Any psychiatric conditions.
Care team	Inclusion	The eligible patients must be under the care of any of the following:
		a) General Practitioner
		b) Community Nurse
Care programs	Inclusion	Participation in one of the following government care programs:
		a) Commonwealth Chronic Disease Management
		b) Commonwealth Coordinated Veterans’ Care Program
		c) NSW Connected Care Program
Unsuitable care programs	Exclusion	Participation in one of the following government care programs:
		a) Commonwealth Extended Aged Care in the Home

For the purposes of our study unplanned admissions are all admissions other than:Admissions from the waiting list (including both the surgical list and the medical waiting list);Admissions listed as "regular same day planned admissions" which are admissions that are intended regular and planned same‒day admissions for an on‒going phase of treatment, such as renal dialysis or chemotherapy.

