Following the signing of a consent form and completion of the Entry Questionnaire, Test patients are connected to the internet and supplied with the TMC Telemonitoring system and trained on its use by the Project Officer (PO) at each site. Their vital signs and questionnaire responses are subsequently monitored on a daily basis by the Clinical Care Coordinator (CCC). On site visits and technical support as well as the obtaining of Consent and the administration of Exit questionnaires are the responsibility of the PO.

Control patients also complete the Entry questionnaire but otherwise continue to receive normal care. For each intervention participant, as many as six control candidates are automatically case matched on gender, age, chronic condition and Socio-Economic Indexes for Areas (SEIFA) [24]. On their consent the two closest matching control candidates commence as participants in the study. The remaining four candidates are held in reserve. Table 2 below demonstrates the case matching process.

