**Table 2 Tab2:** **Example of case matching of Control patients with Test patients**

Test/control	Age	Gender	Major diagnosis	Seifa ^1^ index for postcode	Strength of match (perfect match = 0)
Test	54	M	COPD	1023	
Control	56	M	COPD	1025	1.68^2^
Control	54	F	HD	1022	2.16^3^
Weights	0.2	1	1	0.16	

^1^SEIFA 2011 Socio-Economic Indexes for Areas [24]. SEIFA provides measures of socio-economic conditions by geographic area.

^2^|54-56| × 0.2 + 1 × 0 + 1 × 0 + |1023-1015| × 0.16 = 1.68.

^3^|54-54| × 0.2 + 1 × 1 + 1 × 1 + |1023-1022| × 0.16 = 2.16.

Generally, the closer the match the greater the likelihood of finding a significant result with a smaller number of samples if the impact is relatively small.

Ideally, as many as four matches are sought for each Test patient, and the closest match is then selected as the case matched control for that Test patient. In many cases only one acceptable match may be available.

Following a change of Government in Australia, the requirement to connect patients to the high speed National Broadband Network was removed and as consequence, approximately half of our trial patients will be connected to a variety of NBN, ADSL, ADSL2 and VDSL network services with a minimum level of service of 2Mbps download and 1Mbps upload. Those on the NBN service were guaranteed a download speed of 25Mbit/sec and an upload speed of 5Mbit/sec.

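### The analysis assumes controls identical in major comorbidities, but the matching rule is a nearest-score match on four items that gives comorbidity no weight

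*Protocol article*

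**What the plan says.** Under Classical BACI designs and extensions, the list of assumptions expects blocking on matched controls to deal with the lack of randomisation. It states that "The control patient is generally selected to control for all covariates", and takes this to mean that "control patients should be identical to the intervention patient in terms of age, gender, SEIFA index and major comorbidities". The listed model terms are an overall mean, period, repeated measures within period, group, the period-by-group interaction, an overall slope, and slopes by period and group. No patient covariate is among them.

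The matching rule is described in three places:

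- Abstract: "Control patients are matched according to age, sex, major diagnosis and their Socio-Economic Indexes for Areas (SEIFA".
- Selection of trial participants: "as many as six control candidates are automatically case matched on gender, age, chronic condition and Socio-Economic Indexes for Areas (SEIFA". The two closest consenting candidates enter the study.
- Table 2: a score with weights of 0.2 per year of age, 1 for a gender mismatch, 1 for a major-diagnosis mismatch and 0.16 per SEIFA point, where zero is a perfect match.

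Table 1 accepts patients whose admission codes "indicate a diagnosis for one or more of the following chronic conditions", and lists six condition groups.

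The Data analysis section says that comparisons are valid only on matched pairs, by paired or repeated-measures t-tests, and assigns a one-tailed matched-pair t-test to every test of the intervention. It also plans to test Test-Control differences in the before period.

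**The concern.** The analysis section attributes to the controls a property that the matching rule does not produce. Entry is open to patients with several of the six conditions, so Test and Control patients can share a major diagnosis and still differ in total disease burden. Test patients are selected first by the site Project Officer, and the controls are then drawn from the remaining eligible patients. Nothing in that process ensures that burden balances.

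The protocol itself attributes the trends in its outcomes to the rising burden of chronic disease with age. If patients with more conditions have steeper trends, an imbalance would make Test and Control diverge over time without any effect of telemonitoring. A before/after comparison that does not model the trend would count that divergence as an effect.

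**Working it through.** **1. The plan's own match scores.** Score = 0.2 × (age difference) + 1 × (gender mismatch) + 1 × (diagnosis mismatch) + 0.16 × (SEIFA difference), using absolute differences.

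- Second control: 0.2 × 0 + 1 + 1 + 0.16 × 1 = 2.16. This agrees with Table 2, so the control mismatches on gender and on the major diagnosis itself.
- First control: the footnote's 1.68 follows from its SEIFA value of 1015 (0.4 + 0.16 × 8). The table row gives 1025, which yields 0.4 + 0.16 × 2 = 0.72. This is a separate slip and does not affect the point.

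**2. What the score does with comorbidity.** Comorbidity has no term. With the first control's row values, 0, 1, 2 or 3 extra comorbidities all score 0.72. If age, sex and SEIFA agree, a control with COPD only scores 0, a perfect match, for a Test patient whose major diagnosis is COPD but who also has heart failure and diabetes. Even the major diagnosis can be traded: its 1 point equals 1/0.2 = 5 years of age or 1/0.16 = 6.25 SEIFA points.

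**3. What each analysis does with an unmatched gap.** Least squares was fitted to a noise-free Test-minus-Control series on the log scale. The protocol gives 4.5 years of data, or 54 months. The split into 42 months before and 12 after, and the gaps themselves, are assumptions. Month t runs from 0 to 53.

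| Assumed gap | After-period values only | Before/after, no slopes | Before/after with group-by-period slopes |
|---|---|---|---|
| Constant 0.30 | 0.30 | 0 | 0 |
| Growing 0.01 per month (0.30 at start of intervention) | 0.355 | 0.27 | 0 |
| Curved, 0.0002 × t² | 0.454 | 0.340 | 0.059 in level and 0.011 per month in slope |

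The model as listed is therefore protected against constant and linear gaps. A paired test without slopes is not protected against a linear gap, and neither analysis is fully protected against a curved one.

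**4. Illustrative size for the slope-free before/after paired test.** Let d be the mean Test-Control difference in number of conditions, and g the extra yearly growth in log cost per condition. The period midpoints are half of 54 months apart, which is 27 months for any split. Spurious shift = d × g × 27/12. Both d and g are assumed; the protocol gives neither.

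| d | g = 0.02 | g = 0.05 | g = 0.10 |
|---|---|---|---|
| 0.1 | 0.0045 | 0.011 | 0.023 |
| 0.3 | 0.014 | 0.034 | 0.068 |
| 0.5 | 0.023 | 0.056 | 0.113 |

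For the cost outcomes, Table 6 computes power for a shift of 1 on the log(cost + 1) scale. The grid therefore spans about 0.5% to 11% of that shift.

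**The case against.** The strongest reply is that the design already deals with most of this. The group effect removes a stable difference between Test and Control, and the slopes by group and period remove a linearly growing one. The mixed model was adopted precisely because the standard BACI comparison fails when outcomes trend. That stands. A reader might infer that comorbidity is neither matched nor adjusted for in any way, and the listed terms do not support so broad a statement. The exposure is confined to the slope-free paired tests and to curved divergence. The paired test cannot be set aside, however, because Data analysis names it for every test of the intervention. That section does not say which values are paired.

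The assumption is also hedged, may use major comorbidities loosely for major diagnosis, and does not say that covariates are left out because the matching is exact. That causal link is an inference. An article may also leave the full covariate set to an analysis plan. The point therefore rests on the assumption that is stated, not on the missing covariates. Even under the loose reading, a nearest-score match does not make controls identical, as Table 2 shows. Table 2 is only an example, and does not establish that such a control would be enrolled.

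Two further inferences fail. A reader might compare the grid with the 8% fall in tariff costs in the Background, but that is a result from an external trial and not this plan's target. Nor is it shown that every confidence interval would widen, since a stable comorbidity effect cancels in a before/after change.

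The planned before-period test could reveal divergence, but the article attaches no consequence to it.

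**Conclusion.** The contradiction is established from the text alone and needs no assumed figure. Controls are nearest available matches on four items. They are not identical on those items, and they are not matched on comorbidity at all.

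The consequence is narrower than the contradiction. Bias from unmatched burden can enter the paired t-tests without slopes, and the mixed model only where divergence is non-linear. Its size and direction are unknown. The range of 0.0045 to 0.113 on the log scale rests on assumed values of d and g and on linear divergence. It is small beside Table 6's shift of 1, although that shift is a power-calculation input and need not be the smallest effect of interest. In a non-randomised comparison, the false assumption should be corrected and the residual imbalance adjusted for.

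**What to change.** 1. Reword the assumption to say that each control is the nearest available match on age, sex, major diagnosis and SEIFA, and remove the claims of identity and of matching on major comorbidities.
2. In the mixed model, add the number of Table 1 conditions at entry, from hospital codes and the Entry Questionnaire, with its interaction with time.
3. In the paired analysis, take the Test patient's before-after change minus the mean change of the matched controls, and regress it on the within-set difference in condition count. Add differences in age, sex, diagnosis and SEIFA only where matches are inexact.

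The cost is wording, a few model terms on data already collected, and a few degrees of freedom. Restraint is needed. Condition count, age, sex, six-category diagnosis and SEIFA take 1 + 1 + 1 + 5 + 1 = 9 parameters, or 18 with time interactions, which is heavy against the assumed effective sample size of 30. A linear time interaction will not remove all curved divergence, so the planned plots of before-period differences remain a necessary check. The match score itself need not change.
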